#### Sample estimation

*Sample size for nurse midwives*. The sample size for the intervention and control group of nurse midwives will be obtained by using the formula for comparing two independent samples (intervention group vs control group), guided by the study by Joho [40]. In her study, which is conducted in 39 primary health facilities in Dodoma, she found that the knowledge proportion of nurses on the timing of administration of uterotonic before and after the educational intervention was 44.8% and 63.4%, respectively [40,43].

$$n=2\{Z_{\alpha }\sqrt{[\pi_{0}}(1‐\pi_{0})]+Z_{\beta }\sqrt{[\pi_{1}}(1‐\pi_{1})]\}/{\left(\pi_{1‐}\pi_{0}\right)}^{2}$$

n = Minimum sample size

Zα = Standard normal deviation of 1.96 at 95% confidence interval (CI).

Zβ = Standard normal deviation 0.80 with the power demonstrating statistically significant difference before (baseline) and after intervention between two groups at 80%.

p0 = Proportion of an intervention group at baseline = 44.8% (0.448)

p1 = Proportion after the intervention = 63.4% (0.634)

With a 5% attrition rate:

$$n=2\{1.96\sqrt{\left[0.634(1-0.634)\right]}+0.8\sqrt{\left[0.448(1-0.448)]\right\}}/{\left(0.634‐0.448\right)}^{2})$$

n = 78

So, the minimum sample size will be 78 plus a 5% attrition rate = 82

The ratio of the intervention group to the control group will be 1:2. Therefore, the sample size for the control group will be 164.

Thus, the total sample size in this study will be 246 nurse midwives.

*Sample size for post-CS mothers*. The sample size for the intervention and control group of post-CS mothers will be obtained by using the following formula;

The formula for comparing two independent samples (intervention group vs. control group), and using the proportion of SSI for pre-intervention was 16% and 4.9% for post-intervention [44]. A prospective observational cohort study involving active in-patient and post-discharge surveillance cohort study was done in DRRH at Obstetrics and Gynaecology Department where [43];

$$n=2\{Z_{\alpha }\sqrt{[\pi_{0}}(1‐\pi_{0})]+Z_{\beta }\sqrt{[\pi_{1}}(1‐\pi_{1})]\}/{\left(\pi_{1}‐\pi_{0}\right)}^{2}$$

n = Minimum sample size

Zα = Standard normal deviation of 1.96 at 95% confidence interval (CI).

Zβ = Standard normal deviation 0.8 with the power demonstrating statistically significant difference before (baseline) and after intervention between two groups at 80%.

p0 = Proportion of an intervention group at baseline = 16% (0.16)

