p1 = Proportion after the intervention = 4.9% (0.049)

With a 5% attrition rate:

$$n=2\{1.96\sqrt{\left[0.16(1-0.16)\right]}+0.8\sqrt{\left[0.049(1-0.049)]\right\}}/{\left(0.16‐0.049\right)}^{2}$$

n = 145 plus 5% attrition rate 152

So, the minimum sample size is 145 plus a 5% attrition rate = 152

The ratio of the intervention group to the control group will be 1:2. Therefore, the control group sample size will be 304.

Therefore, the total sample size in this [40] study will be 456 post-CS mothers.

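### The 82 + 164 nurse-midwives give about 77–79% power after attrition, not the stated 80%; power for the 1:2 split should be restated

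*Protocol article*

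**What the plan says.** All of this is in the protocol article, Phase 4, Sample estimation.

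- Significance level: "Zα = Standard normal deviation of 1.96 at 95% confidence interval (CI".
- Power: "Zβ = Standard normal deviation 0.80 with the power demonstrating statistically significant difference before (baseline) and after intervention between two groups at 80" (per cent).
- Proportions for nurse-midwives: "p0 = Proportion of an intervention group at baseline = 44.8% (0.448" and "p1 = Proportion after the intervention = 63.4% (0.634".
- Result: "So, the minimum sample size will be 78 plus a 5% attrition rate = 82".
- Split: "The ratio of the intervention group to the control group will be 1:2. Therefore, the sample size for the control group will be 164".
- Total: "Thus, the total sample size in this study will be 246 nurse midwives".

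The mothers' calculation has the same form, with 16% and 4.9%, n = 145, and 152 after attrition. It ends the same way: "The ratio of the intervention group to the control group will be 1:2. Therefore, the control group sample size will be 304". The total is 456.

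Neither subsection gives a reason for 1:2. The Study population section says that mothers and nurse-midwives will be matched on several characteristics, but does not tie this to the ratio.

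**The concern.** The printed formula has a leading factor of 2 and no allocation term, so it is a formula for two equal groups. Its result is used as the size of the intervention arm, and the control arm is set at twice that. The 80% power is carried over unchanged, although no calculation is shown for the split that will be used.

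If the real power is below 80%, the nurse-midwife knowledge comparison rests on a wrong stated figure. The ratio also deserves a sentence of justification. At a fixed total and similar variances, 1:2 is less efficient than 1:1, so a reader will want to know what the larger control group is for.

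**Working it through.** **1. Reproducing the plan's figures.** The plan's numerical line for nurse-midwives, bracket unsquared and Zβ = 0.80, gives

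n = 2 × {1.96√(0.634 × 0.366) + 0.80√(0.448 × 0.552)} / 0.186² = 2 × (0.9442 + 0.3978) / 0.034596 = 77.6, so 78.

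Then 78 × 1.05 = 81.9, so 82; 2 × 82 = 164; 82 + 164 = 246. For mothers the same form gives 2 × (0.7185 + 0.1727) / 0.012321 = 144.7, so 145. The figures therefore reproduce only with the unsquared bracket. The normal deviate for 80% power is 0.842, not 0.80.

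**2. What a standard formula gives.** Two proportions, pooled, two-sided 5%, 80% power, 44.8% v 63.4%: 112 per arm at 1:1, or 84 + 168 evaluable at 1:2. The plan has 78 + 156 evaluable.

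**3. Nurse-midwife power.** Assumptions: independent participants, p0 taken as the control proportion and p1 as the intervention proportion (the plan labels both as before and after values of the intervention group), two-sided 5%.

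- Pooled: power = Φ[(|p1 − p0| − 1.96 × s0) / s1], where s0 = √{p̄(1 − p̄)(1/n1 + 1/n0)}, p̄ is the overall proportion, and s1 = √{p1(1 − p1)/n1 + p0(1 − p0)/n0}.
- Unpooled: power = Φ[|p1 − p0| / s1 − 1.96].

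For 78 + 156: p̄ = 0.510, s0 = 0.0693, s1 = 0.0675. Pooled: Φ[(0.186 − 0.1359) / 0.0675] = Φ(0.742) = 77.1%. Unpooled: Φ(0.794) = 78.7%.

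For 117 + 117: p̄ = 0.541, s0 = 0.0652, s1 = 0.0640. Pooled: Φ(0.911) = 81.9%. Unpooled: Φ(0.946) = 82.8%.

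| Intervention + control | Pooled | Unpooled |
|---|---|---|
| 82 + 164 (enrolled) | 79.2% | 80.6% |
| 78 + 156 (after 5% loss) | 77.1% | 78.7% |
| 123 + 123 (enrolled) | 83.8% | 84.6% |
| 117 + 117 (after 5% loss) | 81.9% | 82.8% |

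After attrition, exact binomial power for the uncorrected chi-square test is 76.4% at 1:2 and 83.4% at 1:1. With continuity correction it is 73.3% and 79.9%.

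**4. Mothers, 16% v 4.9%.** Pooled power is 95.7% at 152 + 304 and 97.4% at 228 + 228 (94.8% and 96.8% after attrition).

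- Log odds ratio: variance = 1/{n1 p1(1 − p1)} + 1/{n0 p0(1 − p0)}. This is 0.1657 at 152 + 304 (SE 0.407) and 0.1268 at 228 + 228 (SE 0.356). After attrition, the interval around an odds ratio of 0.27 is 0.12 to 0.61 at 145 + 290 and 0.13 to 0.55 at 217 + 217.
- Risk difference: SE is 0.0274 at 152 + 304 and 0.0282 at 228 + 228.

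**The case against.** **The ratio as the cause.** A reader might infer that 1:2 wastes information and is why the nurse-midwife sample misses 80%. The documents do not support that. The plan fixes the intervention arm first and then adds controls. Against that n, doubling the controls raises power from 64.7% (78 + 78, pooled) to 77.1%. The shortfall starts in the formula, and a correct calculation at 1:2 needs only 6 + 12 more evaluable nurse-midwives. Re-splitting 246 is one remedy among others, and it appears only if the total is held fixed.

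**The test.** The planned knowledge analysis is a generalised estimating equation on repeated measures. Its power depends on a within-person correlation that the document does not give. The 80% line is also close: enrolled 1:2 reaches 80.6% unpooled, and 1:1 with continuity correction stops at 79.9%. This limits how firmly 1:1 can be said to pass 80%. It does not rescue the stated figure, because after the plan's own attrition 1:2 falls short on every version computed.

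**Mothers.** A reader might also infer that 1:2 leaves the surgical site infection comparison short of power or precision. Power exceeds 80% under either split. The gain from 1:1 is on the odds ratio scale. The Analysis of SSI section plans a logistic regression for associated factors, but also a difference-in-difference analysis for the intervention effect without fixing its scale. On the risk difference 1:2 is marginally the more precise.

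**Matching and staffing.** In a non-equivalent control design, a larger control pool can serve matching. The plan does not say so, but the possibility stands. No staffing figures show whether 123 nurse-midwives exist at the intervention hospital, or 164 at the control hospital.

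**Conclusion.** The point holds for the stated power of the nurse-midwife sample. On the plan's proportions, two-sided 5%, independent participants and its own 5% attrition, 82 + 164 delivers about 77% (pooled) to 79% (unpooled), not 80%. The gap is small, roughly one to three percentage points. Its cause is the unsquared equal-groups formula with 0.80 as the deviate, followed by doubling the control arm without recomputing power. The same total at 1:1 would give about 82–83%.

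For mothers there is no power failure at 16% v 4.9%. A 1:1 split would reduce the SE of the log odds ratio by about 12% (0.407 to 0.356) and would not help on the risk difference. It is an optional gain. None of this bears on the confounding that comes from having one hospital per arm, which no ratio removes.

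**What to change.** In the nurse-midwife part of Sample estimation, do one of the following:

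- **Keep 1:2 and restate the power**: about 77–79% after attrition, from a formula that includes the allocation ratio, with a reason for the ratio. This costs wording only. If 80% is to be kept at 1:2, 84 + 168 evaluable are needed; adding 5% gives 88.2 and 176.4, so 89 + 177 = 266 enrolled, 20 more than planned.
- **Use 1:1 at the same total**: 123 + 123, about 82–83% after attrition, provided the intervention hospital has that many nurse-midwives. This adds no participants, but 41 more staff are trained there and 41 fewer controls are available for matching.

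In either case, correct the formula (square the bracket, use 0.842).

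For mothers, either give the reason for 152 + 304 or move to 228 + 228. The latter means teaching 76 more mothers at the intervention hospital and recruiting 76 fewer at the control hospital. The choice should follow from whether the odds ratio or the risk difference is the main measure of effect.

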**Fig 3 pone.0287004.g003:**
[figure not shown]
Description of implementation of intervention. Involvement of the hospital administration in interevention phase before enrolling the post CS mothers and nurse midwives to the study.

**Variables definition and measurement. Independent variables:** In this study, the independent variables are socio-demographic characteristics of participants such as age, marital status, education level, past obstetric history, type of operation and economic factors for the post-CS mothers as well as the as age, sex, education level and duration of experience for nurse midwives.

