### Analysis of SSI

Binary logistic regression analysis will be used to assess factors associated with SSI.

The general logistic regression model is given as:

$$\log it[\pi (x)]=\log(\frac{\pi (x)}{1-\pi (x)})=\beta_{0}+\beta_{1}x_{1}+\ldots \ldots +\beta_{p}x_{p}$$

Where *π*(*x*) is the SSI status, *x*_*i*_’*s* is set of independent variables and *β*_*i*_’*s* is their respective parameters.

The power of the study will be set at 80% (0.8) while a confidence interval of 95% with a margin of error of 5% (0.05) was used as a statistical measure of significance (< 0.05 was regarded as significant while > 0.05 not significant).

The effect of intervention between groups will be assessed using difference in difference (DID) analysis.

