## Discussion

The establishment of this guide will also help to cement the need for pre-discharge health education counselling for nurse midives to post-CS mothers and the entire community on home care practices. This will help Ministry of Health to incorporate the guide national wide, with the aim of improving home care after CS na reducing CS complications such as SSI. The limitations of the study include the risk of desirability bias, as participants may not feel comfortable giving honest feedback about their care. This will be prevented by ensuring post CS mothers that their responces will not be shared with their nurse mideives or caretakers hence they should feel free to share them with researcher. Another limitation is the the risk of SSI, which might be increased by other factors like multiple vaginal examinations during labour, time of rupture of membrane, duration of operation, existing medical condition of a woman like HIV/AIDs and diabetes, anaemia status, lack of antibiotics prophylaxis during the pre-and post-operative period and infection in the amniotic fluid. To mitigate this, adequate information regarding labour and operation procedure will be considered from the patient’s file and medical history is recorded from post-CS mothers, which will be used in the inclusion criteria of study participants and data analysis. have been adjusted by the statistical analysis in the statistical model.

The study findings will be published in reputable journals and presented at scientific conferences. The guide produced in this study will be shared with the Tanzania Ministry of Health, for possible adoption on the training of post-CS mothers in health facilities. The final dissertation report will be submitted to MUHAS and UDOM libraries.

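### About 54 SSIs are expected, about 7 of them with the guide: too few for a plain logistic model with all the named covariates, so the SSI analysis should use penalised likelihood and fewer covariates

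*Protocol article*

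**What the plan says.** **Sample size.** Under Sample estimation, the mothers' sample rests on a comparison of two proportions: "p0 = Proportion of an intervention group at baseline = 16% (0.16" and "p1 = Proportion after the intervention = 4.9% (0.049". The result is "So, the minimum sample size is 145 plus a 5% attrition rate = 152" in the intervention arm. A 1:2 ratio then gives 304 controls and 456 mothers in all.

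**Model.** Under Analysis of SSI: "Binary logistic regression analysis will be used to assess factors associated with SSI". The equation printed there is the general logistic model with an unspecified number of covariates. No penalised or exact method is named. The same section assigns the between-group effect of the intervention to difference-in-difference.

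**Covariates.** The variable definitions after Fig 3 state that, for mothers, "the independent variables are socio-demographic characteristics of participants such as age, marital status, education level, past obstetric history, type of operation and economic factors". The next section adds haemoglobin in five classes and reported home care practice (good or poor) as intermediate independent variables. The Discussion lists further SSI risk factors: vaginal examinations, time of membrane rupture, operation duration, HIV, diabetes, anaemia, lack of antibiotic prophylaxis and amniotic infection. A sentence without a subject then says that they "have been adjusted by the statistical analysis in the statistical model".

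**The concern.** The sample size allows for one unadjusted comparison, but the model described for SSI draws on many covariates. With few events per parameter, maximum-likelihood logistic regression pushes odds ratios away from 1. A factor with no SSI among its carriers has no finite odds ratio at all.

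Two outputs are exposed: the adjusted odds ratio for the guide, and the list of factors associated with SSI, which is the stated purpose of the model. If the model fails in use, the obvious repair is to drop variables after seeing the data, and that adds selection bias.

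**Working it through.** **1. The plan's own figure.** Inputs: "Zα = Standard normal deviation of 1.96 at 95% confidence interval (CI"; the value 0.8, entered as the deviate for 80% power; rates 0.16 and 0.049. The printed formula, taken literally, gives

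2 × {1.96 × √(0.16 × 0.84) + 0.8 × √(0.049 × 0.951)} / (0.111)² = 2 × (0.7186 + 0.1727) / 0.012321 = 144.7, so 145.

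Then 145 × 1.05 = 152, 152 × 2 = 304 and 152 × 3 = 456. The form of this formula is a separate matter. An unadjusted comparison of 145 v 290 has about 95% power at these rates, so power is not the problem here.

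**2. Expected SSIs.** Retained controls = 2 × 145 = 290.

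| Scenario | Intervention | Control | Total |
|---|---|---|---|
| Plan's rates, 145 v 290 | 145 × 0.049 = 7.1 | 290 × 0.16 = 46.4 | 53.5 |
| Plan's rates, 152 v 304 | 7.4 | 48.6 | 56.1 |
| No effect, 16% in both | 23.2 | 46.4 | 69.6 |
| Control 11% (low end of the Tanzanian range cited) | 7.1 | 31.9 | 39.0 |
| Control 48% (high end) | 7.1 | 139.2 | 146.3 |

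The 95% binomial range for the intervention arm at 4.9% of 145 is 3 to 13 events.

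**3. Parameters, counted from the named variables.** Arm 1 + six variables in the definitions at one parameter each + five Discussion factors (vaginal examinations, membrane rupture, operation duration, HIV, diabetes) = 12. Anaemia is left to haemoglobin. Lack of prophylaxis and amniotic infection are exclusion criteria. Adding haemoglobin (5 classes, 4 parameters) and practice (1) gives 17.

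Events per parameter: 53.5/12 = 4.5; 53.5/17 = 3.1.

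**4. Effect on the guide's odds ratio.** True OR = (0.049/0.951)/(0.16/0.84) = 0.27, log OR −1.307. A simulation used 1,500 trials per setting at 145 v 290. It assumed binary covariates with prevalence 3-50%, four of them with log odds ratios of 0.3-0.7 and the rest null.

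| Parameters | Mean log OR (ML) | Exaggeration | Coverage | Guide's OR infinite | Some covariate OR infinite |
|---|---|---|---|---|---|
| 5 | −1.366 | 4.5% | 96% | 0.1% | 0.1% |
| 12 | −1.398 | 7% | 96% | 0.1% | 15% |
| 17 | −1.445 | 10.5% | 96% | 0.1% | 32% |

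The last two means correspond to odds ratios of about 0.25 and 0.24. Further simulations with other assumed covariates gave 7-11% exaggeration (OR 0.23-0.25) under maximum likelihood and about 1-3% error under Firth's method, with a root mean square error some 10-16% larger for maximum likelihood.

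**5. Direct check on infinite estimates.** The overall SSI risk is 53.5/435 = 12.3%. If a factor carries no extra risk, the chance of no SSI among its carriers is:
- 3% prevalence (13 mothers): 0.877^13 = 18%
- 5% prevalence (22 mothers): 0.877^22 = 6%
- 20% prevalence (87 mothers): negligible

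Several such factors together raise the chance that at least one fails. Runs with rare covariates gave 15-39%; a run with none below 20% prevalence gave none. For the guide itself, the chance of no event in its arm is 0.951^145 = 0.07%.

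**The case against.** The strongest objection is that no such model is specified. The six variables are introduced as examples, the equation leaves the number of covariates open, and nothing says that haemoglobin and practice enter the SSI model. The Discussion sentence on adjustment has no subject, and the text before it says that the same information will also serve the inclusion criteria. Study population also plans matching on age, type of CS and obstetric history, which overlap three of the six variables. A full analysis plan could shorten the list. This stands: 12 to 17 is a count of named variables, and a reader who inferred that the plan commits to it would go beyond the text. What remains is that the article itself names the model, the candidate variables and an intention to adjust, and its sample size takes no account of them. Removing the three matched variables leaves 9 to 14 parameters, or 5.9 to 3.8 events each, which is still thin.

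Second, difference-in-difference is named for the between-group effect. But the baseline assessment described is of knowledge. Mothers enter after their CS, and no SSI measurement before the intervention is described. For SSI, the logistic model is therefore the only workable adjusted analysis in the article.

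Third, the harm to the main estimate is small. The crude standard error of the log OR is √(1/7.1 + 1/137.9 + 1/46.4 + 1/243.6) = 0.42. The shift of 0.09 to 0.14 is thus about 0.2 to 0.3 of a standard error. This also stands.

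Fourth, more events would ease the problem. At 48% in both hospitals before any effect, and the plan's relative reduction (4.9/16), the total is about 160, or 9 to 13 per parameter. That is true, but the plan is sized on 16%, and lower rates remain thin.

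**Conclusion.** The point holds in a limited form. At the plan's own rates the SSI model would rest on about 54 events, about 7 of them with the guide, against roughly 12 to 17 candidate parameters. Plain maximum likelihood would then exaggerate the guide's log odds ratio by about 7-10%. Nearly half of that or more (about 5%) is present with only 5 parameters, so it reflects the few events in the intervention arm as well as the length of the covariate list.

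The larger practical risk is to the factor analysis: with covariates at about 5% prevalence or less, some odds ratio could be infinite in a sizeable share of trials. The article gives no prevalence for HIV, diabetes or severe anaemia among eligible mothers, so this rests on assumption.

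A reader might infer that the guide's own odds ratio could be infinite, or that its significance test is invalid. Neither is supported: the first has a chance of about 0.1%, and coverage stays near 95%. Maximum likelihood is itself inferred, from plain logistic regression in SPSS with no alternative named.

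**What to change.** In Analysis of SSI:

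- Fit the SSI model by Firth's penalised likelihood with profile-likelihood intervals.
- Use arm and covariates known before discharge only. Leave out reported home practice and follow-up haemoglobin: both are recorded at the postnatal visits, after the education, and do not belong in a model for the guide's effect.
- State the expected number of SSIs (about 7 + 46 at the design rates) beside the sample size, and label the analysis of factors associated with SSI as exploratory.

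The cost is analysis wording, plus an add-on or free software beside SPSS. Estimates will be slightly less favourable to the guide. The change does not cure the confounding that comes from having one hospital per arm.

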#### Sampling and method

A purposive sampling method will be used to select DRRH and SRRH [42]. SRRH and DRRH are both regional hospitals, have specific blocks for maternity care, and offer CEmONC. The intervention has been assigned by hospital settings where DRRH will be selected to be an intervention site because of its higher prevalence of SSI (48%) to post-CS mothers [19], and SRRH will serve as a control site.

Nurse-midwives and post-CS mothers will be selected by using a simple random sampling method [40]. Specifically, lottery replacement methods will be employed where the replacement selection of participants will be done to ensure an equal chance of selection to all until the desired sample size is achieved [40].

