*Assessment and education of post-caesarean mothers*. Before the intervention, the pre-tested tool will be used by the researcher and RA to assess baseline knowledge of post-CS mothers on home care after CS. Both the assessment and intervention of post-CS mothers will be done before discharge. The education intervention about home care will be given in one group depending on the number of post-CS discharged on that day. The intervention will involve slides projection of the post-CS home care and distribution of leaflets with simplified Swahili language and pictures demonstrating recommended home practices after CS. This will be followed by the questions and answers session for more clarification. The intervention will take about 1 hour including a question-and-answer session. This will be performed every day before discharge until the sample size is met. The researcher and other RA (nurse midwives in the profession) will be providing this education to post-CS mothers to ensure the home care guide after CS is delivered effectively. Thereafter, the participants will be instructed to come for the usual recommended post-natal visits to the same facilities for follow-ups that is, on the 7^th^, 14^th^ and 30^th^ day. On the 7^th^ day post-delivery, mothers will be instructed to come for stitch removal, assessment of the wound and other routine post-natal check-up services. In all visits, the post-CS mothers will be requested to report their practices at home, and assess their haemoglobin level to establish their anaemia status using the WHO classification [45]. For the purpose of this study, mothers will be instructed to come down to the facility on the 30^th^ day post-CS to evaluate their prognosis, to assess wound healing and their recovery in general. The wound assessments will be performed by two researchers and research assistants to minimise observer bias. For all wounds with SSI, their samples will be taken for culture to confirm the diagnosis. On the same day (30^th^-day post-delivery), a post-interventional assessment of the knowledge of post-CS home care will be done [46], after being exposed to the home environment.

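### Arm and hospital are the same variable, so the stated 80% power and 5% significance for SSI hold only if the two hospitals do not otherwise differ

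*Protocol article*

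**What the plan says.** **Assignment.** Sampling and method: "The intervention has been assigned by hospital settings where DRRH will be selected to be an intervention site". The reason given is DRRH's higher SSI prevalence (48%). SRRH is the single control site.

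**Sample size.** Sample estimation uses, for nurse-midwives, "the formula for comparing two independent samples (intervention group vs control group", and names the same comparison for mothers. No ICC or design effect enters. The inputs for mothers are "p0 = Proportion of an intervention group at baseline = 16% (0.16", "p1 = Proportion after the intervention = 4.9% (0.049", "Zα = Standard normal deviation of 1.96 at 95% confidence interval (CI" and "Zβ = Standard normal deviation 0.8 with the power demonstrating statistically significant difference before (baseline) and after intervention between two groups at 80". The result is 145, raised to 152 for attrition, with 304 controls.

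**Analysis.** Analysis of SSI specifies binary logistic regression, a 0.05 threshold, "The power of the study will be set at 80% (0.8", and DID for the between-group effect. The knowledge analysis uses generalised estimating equations (GEE), justified by repeated observations on the same person.

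**Delivery.** Intervention: "The education intervention about home care will be given in one group depending on the number of post-CS discharged on that day".

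**Baseline.** Study design (Phase 4) describes a baseline assessment of knowledge in both groups. It describes none of SSI.

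**The concern.** A comparison of DRRH with SRRH contains the effect of the guide and every other difference between the hospitals, and the data cannot tell the two apart. A standard error built from independent mothers covers only the sampling of individuals within each hospital. The variation between hospitals is taken as zero, and one hospital per arm leaves no degrees of freedom to estimate it. The 80% and 5% are therefore stated as properties of the study without the condition on which they depend. The Discussion looks ahead to national adoption of the guide, so a hospital difference read as an effect of the guide, or one that hides such an effect, would have consequences.

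**Working it through.** **1. The plan's own figure.** The printed formula, with the brace not squared, gives n = 2{1.96·√(0.16·0.84) + 0.8·√(0.049·0.951)}/(0.111)² = 144.67, that is 145. The figure reproduces, and its variance is that of independent individuals.

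**2. Power under independence, 152 v 304, 16% v 4.9%.**
- Pooled proportion: (152·0.049 + 304·0.16)/456 = 0.123.
- Null SE: √[0.123·0.877·(1/152 + 1/304)] = 0.0326.
- SE under the alternative: √(0.049·0.951/152 + 0.16·0.84/304) = 0.0274.
- Power: Φ[(0.111 − 1.96·0.0326)/0.0274] = 95.7%.

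The planned numbers therefore have a margin over 80% if independence holds.

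**3. Hospital-level correlation.** The documents give no ICC, so the range below is an assumption. With one hospital per arm, each arm's variance is multiplied by 1 + (n − 1)·ICC. The type I error of the unadjusted test is 2·[1 − Φ(1.96/√R)], where R is the ratio of true to assumed variance. At ICC 0.01:
- The factors are 1 + 151·0.01 = 2.51 and 1 + 303·0.01 = 4.03.
- R = (2.51/152 + 4.03/304)/(1/152 + 1/304) = 3.02.
- 1.96/√3.02 = 1.13, so the type I error is 26%.

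Power repeats step 2 with these factors in both standard errors and the ICC treated as known. The between-hospital SD is √(ICC·0.16·0.84).

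| Assumed ICC | Between-hospital SD (points) | Two-sided type I error | Power, correct variance |
|---|---|---|---|
| 0 | 0 | 5.0% | 95.7% |
| 0.001 | 1.2 | 7.4% | 91.0% |
| 0.005 | 2.6 | 16.7% | 69.2% |
| 0.01 | 3.7 | 25.9% | 49.9% |
| 0.02 | 5.2 | 38.2% | 31.1% |

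**4. Direction.** The ICC model treats the hospital difference as symmetric about zero, but the article says DRRH has the higher SSI prevalence. Suppose the guide does nothing and the true rates are 16% at DRRH and 13% at SRRH (assumed). Then the null SE is √[0.14·0.86·(1/152 + 1/304)] = 0.0345 and the actual SE is √(0.16·0.84/152 + 0.13·0.87/304) = 0.0354.
- Significant apparent harm: Φ[(0.03 − 0.0676)/0.0354] ≈ 14%.
- Significant apparent benefit: Φ[(−0.03 − 0.0676)/0.0354] ≈ 0.3%.

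With SRRH at 11% (assumed), the test is significant about 34% of the time, almost always as apparent harm. If SRRH were the worse hospital, at 25% (assumed), a false benefit would appear about 60% of the time.

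**5. Teaching sessions.** DRRH has about 9016·0.287/365 = 7.1 caesareans a day. With 7 per session and an assumed session ICC of 0.05, the design effect is 1 + 6·0.05 = 1.30, in the intervention arm only. At 1:2 allocation the variance of the difference rises by (1.30·2 + 1)/3 = 1.2. Type I error becomes 2·[1 − Φ(1.96/√1.2)] ≈ 7%, and SSI power remains about 91%.

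**6. SSI interval.** Half-width = 1.96·√[0.1344·(1/145 + 1/290) + 2·SD²], with 16% in both arms and numbers before attrition inflation. It is 7.3 points at SD 0, then 7.8, 9.2, 11.1 and 15.7 points at SDs of 1, 2, 3 and 5 points.

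**The case against.** The article openly calls the design quasi-experimental with a non-equivalent control group, and it plans matching, covariate adjustment and DID. Those measures have value, but matching and adjustment as described act on characteristics of individuals, and a hospital term cannot be separated from arm. DID needs a pre-intervention measurement, which is described for knowledge but not for SSI. Declaring the design non-equivalent does not qualify the 80% and 5% statements.

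Some stronger readings are tempting, and the documents do not support them:

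- **That the stated 80% fails for SSI whatever the ICC.** Power under independence is about 96% and is still 91% at ICC 0.001. It drops below 80% somewhere between 0.001 and 0.005.
- **That group teaching breaks the power.** Step 5 shows it does not at the assumed session ICC. Sessions may also hold fewer than seven study mothers, because mothers are sampled and some are excluded.
- **That knowledge is equally exposed.** A post-only calculation for nurse-midwives (82 v 164, ICC 0.01) gives a type I error of 17%, but it ignores the planned baseline and DID. These remove a stable hospital difference and leave only hospital-specific change over time.
- **That the main risk is a false claim of benefit.** The stated reason for choosing DRRH points the other way.
- **That the 11% to 48% range in the Introduction measures variation between hospitals.** It spans several cited studies, and its upper end equals the figure quoted for DRRH.

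**Conclusion.** The concern stands for SSI. The 80% power, the 5% significance level and the confidence intervals are valid only if the two hospitals would have had the same SSI rate without the guide. The article does not state that condition, the SSI data cannot test it, and the stated reason for choosing DRRH counts against it. At assumed hospital ICCs of 0.001 to 0.02, type I error runs from about 7% to 38% and power from about 91% to 31%. Those figures rest on the assumed ICCs and on a symmetric hospital difference. If DRRH's higher prevalence persists, the likelier errors are a masked benefit or an apparent harm. For knowledge the condition is weaker: no hospital-specific change over time. A reader might infer that the study is invalid without more hospitals. That goes too far: a comparison of these two hospitals can be reported, provided it is described as one.

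**What to change.** 1. In Sample estimation and in the analysis sections, state that the power, confidence intervals and p-values are conditional on no hospital-level difference (for knowledge, no hospital-specific change over time) and refer to individuals within these two hospitals. Withdraw the unqualified 80% and 5% statement.
2. Word the SSI conclusion as a comparison of two hospitals that cannot separate the guide from the hospital.
3. Add a small table of the SSI confidence interval under assumed between-hospital SDs, for example 1, 2, 3 and 5 points. On the planning figures the half-widths are those in step 6 of the working.
4. Optionally, record the teaching session and cluster standard errors on it in the intervention arm. This is a minor refinement and does not cure the hospital-level problem.

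The cost is wording and one table, with no extra hospitals or participants. The price is wider intervals and a more cautious claim. At an SD of 3 points the half-width already equals the planned difference of 16 − 4.9 = 11.1 points.
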